#### Safety

A *χ*^2^ test will be applied to compare the number of SAE between the two groups. Severity and relationship to treatment will be descriptively summarized in tables by group.

### Interim analyses {21b}

An interim analysis is not planned.

### Methods for additional analyses (e.g., subgroup analyses) {20b}

Subgroup analyses are not planned.

### Methods in analysis to handle protocol non-adherence and any statistical methods to handle missing data {20c}

The handling of missing values will be based on the full information maximum likelihood method (FIML) as ITT sensitivity analysis. Further, a per-protocol analysis will be performed on the subsample of participants with complete data and no protocol violation.

### Plans to give access to the full protocol, participant-level data, and statistical code {31c}

To ensure long-term access, data suitable for sharing and future reuse will be kept in citable form (with DOI) for at least 10 years. Data sharing is planned 2 years after the database closure (the final dataset will contain all predefined criteria, scores, and subscales) and after the publication of the primary and secondary outcomes in scientific journals. Open Access will follow the international standard formats, e.g., set out in the “Guidelines on Open Access to Scientific Publications and Research Data in Horizon 2020.”

### Oversight and monitoring

#### Composition of the coordinating center and trial steering committee {5d}

The Centre for Interdisciplinary Addiction Research (CIAR) at the University of Hamburg, Germany, will be responsible for the coordination of the trial. The CIAR prepares and coordinates the tablet-assisted assessments and coordinates the data management across all study sites. CIAR will also support the recruitment for all sites and initiate a continuous exchange of information between the project partners through regular online or in-person meetings at defined project stages and milestones (e.g., implementation, recruitment, and analysis). The PI is responsible for the submission of the formal ethical requests to the independent ethics committee and for the abidance of patient rights. Investigators at the different study sites are responsible for appropriate reporting of serious adverse events (SAE).

#### Composition of the data monitoring committee, its role, and reporting structure {21a}

Data safety is monitored by CIAR at the coordinating site. It will ensure adherence to the protocol and monitor the progress of the trial and provide the funding agency with information and advice, if requested.

#### Adverse event reporting and harms {22}

A serious adverse event (SAEs) for this study is any untoward medical occurrence that is believed by the investigators to be causally related to the study intervention and results in any of the following: life-threatening condition (that is, immediate risk of death), severe or permanent disability, and prolonged hospitalization. SAEs will be collected after the participant has provided consent and enrolled in the study. All SAEs occurring after the entry into the study will be recorded. To ensure participant safety, every SAE, regardless of suspected causality, occurring after the subject has provided informed consent until the subject has stopped study participation, must be reported by the sites to the PI within 24 h of learning of its occurrence. The investigators of the sites take the responsibility for appropriate reporting of SAEs. In case of a SAE, discontinuation will be decided by consensus of PI, local investigator, and the Study Safety Board. The main concern will be the safety of the study subjects.

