### Interventions

#### Explanation for the choice of comparators {6b}

A treatment as usual (TAU) control group is used to compare the experimental intervention to treatments that are already used in clinical practice. Patients in the TAU group will not be offered any additional specific intervention other than the care that they would usually receive from SUD and/or refugee counseling or treatment centers or their general practitioner.

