Quality of life is assessed using the WHO Quality of Life Scale Abbreviated Version (WHOQOL-BREF [37]). The WHOQOL-BREF is a 26-item self-report questionnaire including four domains of quality of life (physical health, psychological health, social relationships, environment), overall quality of life, and general health. It assesses the quality of life of the past 2 weeks on a 5-point Likert scale ranging from 1 to 5. The WHOQOL-BREF has shown good internal consistency, test-retest reliability, discriminant validity, and content validity in different subject samples with and without current health problems [37].

We will monitor and assess (serious) adverse events with a standardized report form during post-intervention and the 3-month follow-up. Any adverse events or reactions that are considered to be related to the intervention will be recorded, managed, and reported to the study coordinator. Serious adverse events will be reported to the ethics committee within 24 h of occurrence, and the study will be terminated prematurely.

The study assessors were trained to conduct the standardized assessment procedures prior to the start of the study.

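### The SAE definition requires a causal link to the study intervention, while the reporting rule and safety tables imply all-cause SAEs, so the content of the tested SAE count is not fixed

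*Protocol article*

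**What the plan says.** In Adverse event reporting and harms {22}, an SAE is "any untoward medical occurrence that is believed by the investigators to be causally related to the study intervention" that also leads to one of three outcomes: a life-threatening condition, severe or permanent disability, or prolonged hospitalization. Death is not named as an outcome. It appears only in the gloss on life-threatening, as immediate risk of death.

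The same section then states that "All SAEs occurring after the entry into the study will be recorded" and that sites must report to the PI "every SAE, regardless of suspected causality, occurring after the subject has provided informed consent until the subject has stopped study participation".

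The Safety section under Statistical methods plans that a chi-square "test will be applied to compare the number of SAE between the two groups". It adds: "Severity and relationship to treatment will be descriptively summarized in tables by group".

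For adverse events more widely, Plans for assessment and collection of outcomes {18a} says: "Any adverse events or reactions that are considered to be related to the intervention will be recorded".

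On the control arm, Explanation for the choice of comparators {6b} says: "Patients in the TAU group will not be offered any additional specific intervention other than the care that they would usually receive". On blinding, Procedure for unblinding {17b} states that only the data adjudicators stay blinded and that the remaining study personnel are not.

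**The concern.** A between-arm comparison of harms needs one rule, applied in the same way in both arms, for what counts as an event. Here the term SAE carries a causality condition that refers to an intervention only one arm receives. Taken at its word, the definition makes a hospitalized man in STARC-SUD an SAE if the investigator suspects the group sessions. It can never make a hospitalized man in TAU an SAE.

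The error can run in either direction. If investigators attribute some background events to the sessions, STARC-SUD shows an excess that is not real. If they attribute none, the count is 0 v 0 whatever the true difference. In both cases the result turns on the judgement of people who know the allocation.

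The problem sits in a data-capture rule. An event that a site does not classify as an SAE may never be entered, and an analysis plan written later cannot recover it. Six regions working from the same text could also resolve the contradiction differently. The chi-square test is the only inferential safety analysis that the article describes.

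**Working it through.** **1. Setting the statements side by side**

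| Statement | Section | Can an unrelated event be an SAE? |
|---|---|---|
| Definition: believed causally related to the study intervention | {22} | No |
| Reporting: every SAE, whatever the suspected cause | {22} | Yes |
| Relationship to treatment tabulated by group | Safety | Yes; otherwise the table has nothing to show |
| Adverse events considered intervention-related are recorded | {18a} | Points to no, but concerns adverse events generally |

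These cannot all hold. The reporting sentence does not settle the matter on its own, because it governs SAEs, a term the same section has already restricted to related events.

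**2. Number per arm**

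Sample size {14} gives 100 per group and 30% dropout: 100 / 0.70 = 142.9, so 143 per arm and 286 in total. This reproduces the stated figure. The article gives no SAE rate, no fraction judged related and no repeat-event rate. All three are assumptions below. The two-sided 0.05 level is stated for the primary analysis and assumed here for the safety test.

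**3. Literal definition, TAU fixed at zero**

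For *a* v 0 with 143 per arm, the uncorrected Pearson statistic reduces to 286*a* / (286 − *a*).

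| STARC-SUD v TAU | Chi-square | p | Fisher exact p |
|---|---|---|---|
| 3 v 0 | 858 / 283 = 3.03 | 0.082 | 0.247 |
| 4 v 0 | 1144 / 282 = 4.06 | 0.044 | 0.122 |
| 7 v 0 | 2002 / 279 = 7.18 | 0.0074 | 0.0145 |

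Four events judged related are enough to reject.

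**4. Probability of a false signal under the literal definition**

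Let the true all-cause risk *p* be the same in both arms, and let a fraction *f* of STARC-SUD events be judged related. The test rejects when X ≥ 4, with X ~ Binomial(143, *pf*).

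| Assumed *p* | *f* = 0.25 | *f* = 0.50 |
|---|---|---|
| 2% | 0.006 | 0.056 |
| 5% | 0.105 | 0.481 |
| 10% | 0.481 | 0.931 |
| 15% | 0.788 | 0.995 |

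At *p* = 5% the expected related count is 143 × 0.05 × 0.25 = 1.8 or 143 × 0.05 × 0.50 = 3.6.

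**5. All-cause reading**

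With 5% true risk in each arm, about 7 of 143 men are affected per arm (143 × 0.05 = 7.15). The expected table is then 7 v 7, with no built-in difference. For participants with at least one SAE and equal risk of 2% to 15%, the type I error of the uncorrected chi-square test, by exact enumeration, is 0.046 to 0.051.

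**6. If the number of SAE were taken as events**

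Repeats within a man raise the variance of the event total. If the variance/mean ratio is φ, a test that ignores this has type I error of roughly 2[1 − Φ(1.96 / √φ)].

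- φ = 1.5: 1.96 / 1.225 = 1.60, giving 0.11.
- φ = 2: 1.96 / 1.414 = 1.39, giving 0.17.

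Simulation with negative-binomial counts (40,000 runs, mean 0.1 or 0.2 SAEs per man) gives 0.11 at φ = 1.5, 0.16 to 0.17 at φ = 2, and about 0.05 with no clustering.

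**The case against.** The strongest reply is that one clause is being read against the rest of the text. Recording of all SAEs after entry, reporting without regard to causality, and tabulating relationship by group are the operational statements, and all three fit all-cause capture in both arms. On that reading TAU can have SAEs and the test is fair. This stands as far as it goes. A reader might infer from the definition that TAU can have no SAE at all and that the comparison is biased by construction, but the documents do not support that. They support a contradiction, with bias only if the definition is what sites apply. The reply does not remove the contradiction, because the definition is still what a site would consult to decide whether an event qualifies.

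A reader might also infer that the test treats several events in one man as independent. The Safety section does not name its unit. A two-group chi-square test needs a with/without classification, so participants with at least one SAE is a natural reading, and the choice of unit could be left to an analysis plan. The inflation in step 6 is therefore conditional and is not a defect of the stated plan.

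Three smaller objections also stand:

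- The {18a} sentence concerns adverse events and reactions generally, so it is weak evidence about the tested SAEs.
- A fatal event would probably be reported as life-threatening, so the absence of death from the list is a wording gap with no demonstrated effect.
- The false-signal probabilities depend heavily on assumed inputs. At 2% risk with a quarter judged related, the figure is 0.006.

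**Conclusion.** The concern holds as an internal contradiction: the article does not fix whether the SAEs it will test are all-cause or intervention-related only. Under the literal definition the TAU count is zero by rule, and the comparison measures an unblinded causality judgement. At an assumed equal true risk of 5%, with a quarter to a half of STARC-SUD events judged related, the false-rejection probability is about 0.11 to 0.48 against a nominal 0.05. Over the wider assumed grid it runs from 0.006 to 0.995. Under the all-cause reading there is no such bias.

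This should be fixed because it is a capture rule that cannot be repaired after the data are collected. It does not threaten the primary endpoint or the sample size, and no interim analysis is planned that could depend on it.

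**What to change.** Reconcile the definition in {22}, the Safety section and the adverse-event sentence in {18a}:

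- Remove causality from the SAE definition. Define an SAE by its outcome alone and name death explicitly.
- State that SAEs are sought and recorded in the same way, over the same period, in both arms.
- Record the investigator's causality judgement as a separate attribute of each event. The planned table of relationship to treatment then has a meaning.
- State that the between-arm comparison is of participants with at least one SAE, using an exact test if counts are sparse, and that event counts are reported descriptively.

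The cost is protocol wording, matching wording in any analysis plan, and a check that the e-CRF and report form do not screen on relatedness. Events already collected should be checked for which rule each site applied, since the article says recruitment has begun. The downside is that more events, including unrelated ones, may be recorded in both arms.

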#### Criteria for discontinuing or modifying allocated interventions {11b}

In case of a serious adverse event, the PI will decide together with a Study Safety Board if the treatment needs to be discontinued. Participants are free to discontinue or modify the allocated intervention at any time of the study. In case of worsening disease (e.g., acute suicidality), the study personnel will consult the participant on additional necessary treatment and referral options.

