#### Sample size {14}

*N* = 286 participants are planned to be included in the study. An earlier RCT comparing a transdiagnostic group intervention for refugees vs. treatment as usual found a greater reduction in psychological distress (as measured by GHQ-12) in the intervention group compared with the control group, with a medium effect size of *d* = 0.57 in the change from baseline to 3-month follow-up [23]. A pilot study of STARC showed that the recruitment of refugees with psychological distress was feasible, with about 85% of the screened patients being eligible for the study [9].

In a previous study evaluating the effects of an integrated present-focused treatment of SUD and PTSD, we found a greater reduction in psychological distress (as measured by SCL-27) in the intervention group compared with the control group, with a mean effect size of *d* = 0.39 [6]. On the basis of these results, we assume a small to medium effect size of *d* = 0.40 for STARC-SUD compared to TAU in a sample of refugees with SUD and co-occurring psychological distress. To detect between-group differences of an effect size of *d* = 0.40 (*α* = 0.05; power = 0.80), 100 participants per group are required. To account for a dropout rate of 30%, we aim to recruit 286 participants.

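### The closed SAE list names neither death nor initial hospitalization, so deaths are left to interpretation and ordinary-length admissions can go unreported and uncompared

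*Protocol article*

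**What the plan says.** The definition in Adverse event reporting and harms {22} has two parts. An SAE is "any untoward medical occurrence that is believed by the investigators to be causally related to the study intervention", and it must be one that "results in any of the following: life-threatening condition (that is, immediate risk of death), severe or permanent disability, and prolonged hospitalization". That gives three seriousness criteria and no open-ended final item.

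The same section then requires sites to report to the PI, within 24 hours of learning of it, "every SAE, regardless of suspected causality, occurring after the subject has provided informed consent until the subject has stopped study participation". Discontinuation after an SAE is to be agreed between the PI, the local investigator and the Study Safety Board.

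The Safety section under Statistical methods states that a chi-square "test will be applied to compare the number of SAE between the two groups". No other safety quantity is tested between arms.

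Plans for assessment and collection of outcomes {18a} covers adverse events more widely, but with a condition: "Any adverse events or reactions that are considered to be related to the intervention will be recorded, managed, and reported to the study coordinator". It also says that SAEs go to the ethics committee within 24 hours and that the study will then be ended early.

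Criteria for discontinuing or modifying allocated interventions {11b} gives its own example of deterioration: "In case of worsening disease (e.g., acute suicidality), the study personnel will consult the participant on additional necessary treatment and referral options".

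**The concern.** One definition does three jobs. It decides what a site reports urgently, what the PI and Safety Board look at, and what enters the between-arm safety test. An event outside the list drops out of all three.

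The list omits death as a named outcome and admits hospitalization only in its prolonged form. The participants are trauma-exposed men with marked distress and hazardous substance use or SUD (Eligibility criteria {10}), and {11b} itself names acute suicidality as the example of worsening. A short admission for such a crisis is a foreseeable event here. Six metropolitan regions take part (Study setting {9}), so sites may also settle the unlisted cases differently, and the counts would then not be comparable across sites.

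This is not detail left to a fuller document. The article states a definition specific to this study, and the objection is to what that definition says.

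**Working it through.** The protocol states no SAE rate or other safety figure, so there is no number to reproduce. The check is a reading of the text, followed by an illustration under assumed rates.

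**1. Event types against the three criteria in {22}** (causality condition set aside for now)

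| Event | Criterion met | Result |
|---|---|---|
| Overdose, suicide attempt or withdrawal with immediate risk of death | life-threatening | SAE, admitted or not |
| Death preceded by a recognised life-threatening state | life-threatening, by inference | countable, but only by interpretation |
| Death with no such state observed | none named | left to the site |
| Long new admission, not life-threatening | depends on whether *prolonged* means a long stay or an extended one | unclear |
| Ordinary-length new admission, e.g. suicidal crisis, no immediate risk of death, no disability | none | not an SAE |

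**2. Does another section recover the last row?**
- {18a} records other adverse events only if they are considered related to the intervention, and attaches no test.
- {11b} provides for consultation and referral, not for reporting.
- The reporting rule in {22} drops causality, but it applies to SAEs, that is, to events that already meet the definition. It adds no outcome to the list.

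So the last row is not recovered unless the event is thought related to the intervention, and even then it does not enter the Safety comparison.

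**3. Two neighbouring conflicts that the repair touches**
- *Causality.* The definition requires a believed causal link to the study intervention, while the reporting rule disregards causality. TAU participants do not receive that intervention, so on a literal reading almost no TAU event can qualify, whatever the seriousness list says.
- *Stopping.* {18a} says the study ends early after an SAE, whereas {11b} and {22} provide for a joint decision. If the list is widened while both statements stand, more events meet the condition in {18a}.

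**4. Illustration only; every rate below is an assumption**

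Number of admissions, if 5% to 10% of 286 men have an acute admission:
- 286 × 0.05 = 14.3 and 286 × 0.10 = 28.6, so about 14 to 29 admissions.
- If half to three quarters are not prolonged: 286 × 0.05 × 0.5 = 7.2 and 286 × 0.10 × 0.75 = 21.5, so about 7 to 21 admissions.
- These lean high, because some would qualify as life-threatening and the causality condition would exclude others anyway.

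Effect on the between-arm test, with 286 / 2 = 143 per arm, two-sided alpha 0.05, and a fraction f of serious events captured equally in both arms. With p1 and p2 the captured rates and p̄ their mean:

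power ≈ Φ{ [ |p1 − p2| − 1.96·√(2p̄(1 − p̄)/143) ] / √( [p1(1 − p1) + p2(1 − p2)]/143 ) }

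| f | true rates 10% vs 4% | true rates 8% vs 2% |
|---|---|---|
| 1.00 | 0.51 | 0.65 |
| 0.75 | 0.40 | 0.52 |
| 0.50 | 0.28 | 0.37 |
| 0.25 | 0.16 | 0.21 |

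Worked line for f = 0.50, 10% vs 4%: p1 = 0.05, p2 = 0.02, p̄ = 0.035; (0.03 − 1.96 × 0.0217)/0.0217 = −0.58; Φ(−0.58) = 0.28. The normal approximation is rough at such low counts. The table shows the direction of the effect, not its size in this trial.

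**The case against.** A reader might infer that every death and every emergency admission for overdose, suicidality or withdrawal falls outside the definition. The text does not support that. Any such event with immediate risk of death meets the first criterion, whether or not the man is admitted and for however long. Many deaths could be entered the same way. *Prolonged* can also be read to cover a long first admission. For death, then, the fault is an outcome left to interpretation, not a certain exclusion. For admissions, it is confined to those of ordinary length that are not judged life-threatening or disabling.

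A reader might also take 7 to 21 as the number of events lost. The admission rates and the non-prolonged share have no source in the protocol, so that range is not an estimate.

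It can also be said that {18a} provides a standardized report form. The form is not shown, so its content cannot be judged. The text of {18a} limits recording of other adverse events to those considered related to the intervention.

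The strongest objection is to repairing the list alone. The causality condition would still keep most events out, especially under TAU, and the early-termination statement in {18a} would, read literally, apply to each newly listed admission. That objection stands. It bears on how the repair is made and does not remove the gap in the list.

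**Conclusion.** The point holds in a limited form. The closed list names neither death nor initial inpatient hospitalization, and no other section supplies them. Because SAE status controls the 24-hour reports, Safety Board involvement and the only between-arm safety test, applying the text as written can miss serious events or count them inconsistently. This is a rule fixed badly, not a missing detail.

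The number of events affected cannot be estimated from the protocol. A narrower definition can be expected to weaken the safety comparison, but by how much depends on event rates that the protocol does not give. The sample size and the primary analysis are unaffected.

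The conclusion rests on a literal reading of {22}, and on no unseen document, such as the report form, widening the list.

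**What to change.** In Adverse event reporting and harms {22}, add death and inpatient hospitalization, initial or prolonged, to the seriousness list. Use the identical list on the standardized report form and in the Safety comparison.

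Make two reconciliations in the same amendment:
- The causality condition in the definition with the reporting rule that disregards causality, both in {22}, stating which set of events the between-arm test counts.
- The early-termination statement in {18a} with the discontinuation decisions in {11b} and {22}, so that the wider list does not by itself change what stops the study. Which of these rules should apply is for the sponsor and investigators to settle.

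Listing suicide attempt as a separate item is optional; nothing in the protocol requires it.

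The change is one of wording in the protocol and the form, but the list should not be amended without the two reconciliations. The downside is somewhat more SAE reports, including admissions due to the underlying SUD. Trial status gives September 2020 as the start of recruitment, so events already recorded would need to be classified again under the new list; otherwise the comparison would mix two definitions.
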